### Outpatient visit

At the single outpatient study visit between six to eight weeks, the following parameters are assessed; current NRS-pain; analgesic use; mobility status by the TUGT, de Morton Mobility Index (DEMMI) and the Short Physical Performance Battery (SPPB); current living situation (rehabilitation or at home); wound status and complications (thrombosis, consolidation, infection, readmission). Furthermore the self-assessment health questionnaires EuroQol(EQ)-5D-3 L and Short Form (SF)-12 are completed. If not administered during admission the MMSE is completed (Table 4).

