**Methods/design:**

One hundred and sixty patients with an intra or extracapsular hip fracture scheduled for internal fixation (intramedullary hip nail, dynamic hip screw or cannulated screws) or prosthesis surgery (total hip or hemiarthroplasty) will be included in this prospective, open-label, parallel, multicenter, randomized controlled, clinical superiority trial. Patients will be allocated to two treatment arms: group ‘A’ will be treated with continuous-flow cryocompression therapy and compared to group ‘B’ that will receive standard care. Routine use of drains and/or compressive bandages is allowed in both groups. The primary objective of this study is to compare acute pain the first 72 h postoperative, measured with numeric rating scale for pain. Secondary objectives are: (non-) morphine analgesic use; adjusted postoperative hemoglobin level; transfusion incidence; incidence, duration and severity of delirium and use of psychotropic medication; length of stay; location and duration of rehabilitation; functional outcome; short-term patient-reported health outcome; general and cryotherapy related complications and feasibility.

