## Background

Hip fractures are one of the most important causes of long-term disability and a significant public health issue [1]. Incidence varies on a global scale [2, 3] but incidence is estimated to vary between 414 and 957 per 100,000 inhabitants in the USA [4]. Due to aging of the population in general a significant increase in hip fracture numbers is expected [5].

Hip fractures are a serious condition associated with high morbidity, one-year mortality rates up to 29 % [2, 4], severe pain [6, 7] and significant decline in functional status [8–11]. Less than 50 % of (semi-) independent living elders return to their pre-fracture habitat [11, 12]. Among the most serious of complications is the onset of delirium, which has a particular high incidence of 45 % in hip fracture populations [13–15]. Possibly because this condition is known to be extremely painful [15–18] and patients with pain are nine times more likely to develop a delirium [18–20] and furthermore take longer to ambulate and consequently, have longer length of stay [9].

Upon admission 40 % of hip fracture patients is anemic [21] and observed intraoperative blood loss is systematically underestimated; up to six-fold in excess in extracapsular fractures [22]. The continued postoperative decline in hemoglobin levels results from, among others, surgical site bleeding [22]. This yields a specifically high transfusion rate in this frail elderly patient category where use anticoagulants or thrombocyte aggregation inhibitors is relatively prevalent [23]. Besides (postoperative) surgical site bleeding, the fracture trauma and subsequent surgical stabilization procedure induce a inflammatory response causing leakage of plasma proteins and migration of inflammatory cells that lead to local peripheral vasodilatation and increased capillary permeability, ultimately causing edema [24]. Edema gradually develops during the first week post surgery, is more pronounced in intertrochanteric fractures and correlates well with reduced knee extension strength and functional performance [25, 26]. In an attempt to reduce edema and postoperative hemorrhaging compressive wound dressings are applied [27–29]. Dynamic pneumatic compressive devices not only reduce blood loss, edema and offer a better (hemo) dynamic profile in the deep venous and lymph system, it also exerts analgesic effects and reduces the inflammatory response when combined with a cryotherapy adjunct [30–35].

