**Table 4 Tab4:** Outcome assessment points

		Assessment point						
Item	Data collection instrument (unit)	Baseline (A&E department)	Day of surgery	24 h	48 h	72 h	Discharge	6 - 8 weeks (outpatient clinic visit)
Demographics	-	X						
Pre-fracture functional status	NMS, KATZ-ADL	X						X
Delirium risk assessment	DRAS	X						
Cognitive function	IQ-CODE	X						
	MMSE						X	X
Blood loss	Intraoperative loss *(cc’s)*		X					
	Drain output^a^ *(cc’s)*			X	X	X	X	
Outcome								
Pain	NRS	X	X	X	X	X	X	X
Analgesics	Acetaminophen	X				X	X	
	NSAID’s	X				X	X	
	Morphine	X				X	X	
Blood loss	Hemoglobin (mmol/l)	X		X		X		
Transfusion incidence	Number of units						X	X
Delirium	DOS-score	X	X	X	X	X	X	
	DRS-R-98^c^		X	X	X	X	X	
	Pyschotropic medication	X				X	X	
Length of stay^b^	*(Hours)*						X	
Functional outcome	TUGT						X	X
	DEMMI							X
	SPPB							X
	Rehabilitation location						X	X
	Rehabilitation duration						X	X
PROM	EQ-5D-3L							X
	SF-12							X
	Satisfaction questionnaire						X	
Complications	General						X	X
	Therapy related						X	X
Feasibility	Nurse staff questionnaire						At discharge of last patient	

*A&E* accident and emergency, *NMS* New Mobility Score, *IQCODE-N* Informant Questionnaire on the Cognitive Decline in Elderly patients, *MMSE* Mini Mental State Exam, *NRS* numeric rating scale, *PC* packed cells, *DOS* Delirium Observation Screening, *DRS-R-98* Delirium Rating Scale Revised 98, *TUGT* Timed Up and Go Test, *DEMMI* De Morton Mobility Index, *EQ-5D-3*
*L* EuroQol questionnaire, *SF-12* Short Form-12 questionnaire

^a^Including autologous reinfusion. ^b^Start count at admission and at the end of surgery. ^c^: administered when DOS ≥ 3

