## Statistics

### Analysis of outcome parameters

All statistical analyses will be computed using the SPSS statistical package (IMB SPSS, Inc., Release 20.0.0.0, 64-bit edition). Statistical analysis will be performed according to the intention-to-treat principle. Baseline characteristics will be described in accordance with CONSORT guidelines [41] using means and standard deviation in case of normal distribution, and medians and interquartile ranges otherwise. Continuous variables will be checked for normality, visually and by using the Shapiro Wilk test. Our primary analysis focuses on the differences in NRS-pain scores between the study groups 24 h postoperative and will be analyzed by use of Student’s T or Mann–Whitney U tests in case of skewed distribution. To assess treatment effect over time, a mixed model analysis for repeated measures will be performed. This model allows missing data and adjustment for serious confounders and interactions. In case of skewed distributions and outliers non-parametric variants will be used (e.g. Mann Whitney U or Friedman tests). Secondary continuous outcome measures (EQ-5D-3L, SF-12, DRS-R-98 and hemoglobin) will be compared by use of Student’s t or Mann Whitney U tests. Ordinal variables will be analyzed using the Mann–Whitney test. Chi-squared tests will be performed in case of categorical variables. In case of important confounding, analysis will be adjusted to correct for these factors (by use of multiple regression analysis, linear or logistic). A *p*-value of < 0.05 will be considered statistically significant.

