### Sample size calculation

Sample size calculation is based on the primary outcome measure, NRS-pain at 24 h postoperatively. Subsequently, a mean NRS-pain score for postoperative day one was drawn from the Spaarne Gasthuis electronic patient dossier digital databanks and a standard deviation of 2.2 was calculated for pooled internal fixation and (hemi) arthroplasty for cervical and peritrochanteric fractures. The minimal clinical relevant difference for NRS-pain is 1.3 out of 10 [53]. The alpha was set at 5 % with a power of 90 % due to anticipated heterogeneity in regard to operating techniques, general care protocols but predominantly in regard to pain protocols between the participating centers (Table 2). An expected NRS failure rate of 10 % is anticipated together with expected missing data a drop out of 22.3 % is computed. The total number of included patients will be 160.

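### Rehabilitation duration is last seen at one visit in a 6-8 week window, so unfinished durations are right-censored at varying times, and no method named in the statistics section handles censoring

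*Protocol article*

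**What the plan says.** The abstract lists "location and duration of rehabilitation" among the secondary objectives. The Aim section repeats the item and describes it as short-term.

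Table 4 marks "Rehabilitation duration" at discharge and at 6-8 weeks, with nothing later. On the last contact, the Outpatient visit section says: "At the single outpatient study visit between six to eight weeks, the following parameters are assessed". For rehabilitation, that section names only the current living situation, in rehabilitation or at home. It names no date on which rehabilitation ended.

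Under Analysis of outcome parameters, the methods named are the t-test, Mann-Whitney, Friedman, chi-squared, a repeated-measures mixed model, and linear or logistic regression. The sentence on continuous secondary outcomes reads "Secondary continuous outcome measures (EQ-5D-3L, SF-12, DRS-R-98 and hemoglobin) will be compared by use of" t or Mann-Whitney tests. Rehabilitation duration is not in its list, so no test is assigned to it by name.

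**The concern.** The visit has a category for patients still in rehabilitation, so the protocol expects some. Their true duration is unknown, and the lower bound depends on when they happen to be seen. Take rehabilitation starting on day 10 (an illustration, not a protocol figure). A patient still there at the visit is recorded at 42 - 10 = 32 days if seen on day 42, and at 56 - 10 = 46 days if seen on day 56. A patient who finishes on day 50 counts as unfinished at 32 days on the early visit and as complete at 40 days on the late one.

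If these values are compared as if complete, the longer durations are clipped. Clipping affects the arm with slower recovery more, so the difference shrinks. If unfinished patients are treated as missing, the comparison is among early finishers, a group selected after randomisation. In either case, a null result on rehabilitation could reflect the length of observation and not the treatment.

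**Working it through.** **The plan's own figure.** The only sample-size calculation concerns pain: "The alpha was set at 5 % with a power of 90" %, "a standard deviation of 2.2 was calculated for pooled internal fixation and (hemi) arthroplasty", and "The minimal clinical relevant difference for NRS-pain is 1.3 out of 10". With a two-sided test assumed,

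n per arm = 2 × (1.960 + 1.282)² × 2.2² / 1.3² = 60.2, so 61 per arm and 122 in total.

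With 22.3 % drop-out, 122 / 0.777 = 157.0, so 158. The t-based version needs 62 per arm, and 124 / 0.777 = 159.6, so 160. The stated total reproduces. It does not involve rehabilitation and is untouched by this point.

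**Inputs for the check.** From the protocol: last observation at 6-8 weeks, 160 patients, 1:1 allocation (80 per arm). The protocol gives no expected duration, no unfinished share and no expected effect. The following are therefore assumptions: Weibull durations with shape 1, 1.5 or 2; treated durations 0.75 times control; visit uniform over weeks 6-8; control share unfinished at week 7 from 10 % to 70 %; durations counted from surgery; no drop-out.

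**Hand check (shape 1, 30 % unfinished, cut-off fixed at 7 weeks).**
- Control mean = 7 / (-ln 0.30) = 5.81 weeks. Treated mean = 0.75 × 5.81 = 4.36. True difference = 1.45.
- The mean truncated at c is mean × (1 - S(c)). Control: 5.81 × 0.70 = 4.07. Treated: S = exp(-7 / 4.36) = 0.20, giving 3.49. Difference = 0.58, or 40 % of the truth.
- The mean among completers is mean - c × S / (1 - S). Control: 5.81 - 3.00 = 2.81. Treated: 4.36 - 1.76 = 2.60. Difference = 0.21, or 15 %.

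The simulation gives 40 % and 15 % for the same case.

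**Share of the true mean difference kept (range over the three shapes).**

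| Controls unfinished | Truncated at visit | Unfinished dropped |
|---|---|---|
| 10 % | 74-88 % | 43-62 % |
| 20 % | 54-75 % | 24-43 % |
| 30 % | 40-63 % | 15-31 % |
| 50 % | 19-39 % | 5-15 % |
| 70 % | 6-19 % | 1-5 % |

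**Power, 80 per arm, shape 1.5.**

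| Controls unfinished | Mann-Whitney, full follow-up | Mann-Whitney, truncated | Mann-Whitney, completers | Log-rank, censored |
|---|---|---|---|---|
| 10 % | 0.64 | 0.64 | 0.37 | 0.74 |
| 30 % | 0.66 | 0.61 | 0.16 | 0.67 |
| 50 % | 0.66 | 0.48 | 0.08 | 0.56 |
| 70 % | 0.64 | 0.24 | 0.05 | 0.37 |

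Mann-Whitney on durations capped at a common 6 weeks has power 0.63, 0.59, 0.49 and 0.31 in the same rows. Up to 50 % unfinished, this is within 0.02 of the truncated values. At those shares, the gain from a common horizon is a clearly defined quantity and not extra power.

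**The case against.** **The aim is short-term.** A duration restricted to the first weeks is a legitimate target, and measured against it the unrestricted mean difference is not something lost. This stands as far as it goes. But a restricted duration needs one horizon for everyone, and a 6-8 week window gives each patient a different one.

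**The analysis plan may settle it.** A reader might infer that the protocol commits to complete-value tests for this outcome. It does not: rehabilitation duration is in no test's list, and a plan not shown may assign a suitable method. What remains is that the last observation point is fixed here, the visit text names status and not an end date, and none of the methods listed fits such data.

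**The loss may be small.** A reader might also infer that most of any benefit would vanish. That requires an unfinished share the document does not give. At 10 % unfinished, truncation keeps about three quarters or more of the difference, and Mann-Whitney on truncated values loses little power up to about 30 %. The worst figures require dropping unfinished patients, which the protocol does not propose and which would sit badly with its intention-to-treat principle.

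**The Background figure does not supply the share.** Fewer than half of (semi-)independent elders are said to "return to their pre-fracture habitat", but no time point is given. Failing to return can also mean permanent nursing-home placement or death. More relevant is the Discussion's remark that patients barred from weight bearing at discharge are first allowed it at the outpatient visit. This makes unfinished rehabilitation foreseeable, though not countable.

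**Conclusion.** The point holds in a limited form. Rehabilitation duration is right-censored for patients still in rehabilitation at the single visit, at a cut-off varying by up to 14 days, and the listed methods do not deal with this.

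The consequence is conditional. With truncated values, more than half of the mean difference is lost only once roughly 20-40 % or more of controls are unfinished, depending on the shape of the distribution. If unfinished patients are dropped, more than half is lost from about 20 % upward in every shape tried. These sizes rest on the assumed Weibull durations and the assumed 25 % shortening; the protocol supports neither figure nor contradicts it.

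This is one secondary outcome. The primary pain comparison and the total of 160 stand. A suitable method is cheap, so the change is worth making before the data are analysed.

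**What to change.** 1. At the outpatient visit, record the date on which rehabilitation ended, or that it is ongoing. State the starting point of the clock.
2. Analyse time to end of rehabilitation, censored at the visit date for patients still in rehabilitation, by Kaplan-Meier with a log-rank or Cox comparison stratified by surgery group (internal fixation or arthroplasty). Alternatively, compare the restricted mean to a common day 42, which suits the short-term aim.
3. Include all randomised patients and not only those who attend. For non-attenders, obtain the end date from records or censor at last contact.
4. Treat death as a competing event, and define how permanent nursing-home placement counts. Keep the event as end of rehabilitation: living at home is a different outcome, which a patient placed permanently in a nursing home would never reach.

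The cost is one extra date field and a few lines of analysis text. The result becomes a hazard ratio or a restricted mean in place of a simple mean duration. Power for this outcome may still be modest: with shape 1.5, the log-rank test reaches 0.67 at 30 % unfinished and 0.56 at 50 %.

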### Data collection and handling

Upon inclusion patient characteristics are entered in RM and postoperative randomization takes place. A unique patient number is generated by RM, which will be used for further data collection on preformatted case report forms (CRF’s). Only the coordinating investigator has access to the key-file that can identify patients from RM-generated patient numbers, it will be stored at the coordinating center throughout and after completion of the trial and will not be shared. The Spaarne Gasthuis is the unrestricted owner of the final dataset; no contractual agreements exist in regard to publication policies. No interim analysis will be performed.

### Data management team

The coordinating center comprises of: the principal investigator, the coordinating investigator, a research nurse, a research assistant, a clinical epidemiologist and statistician. The research assistant enters data in RM. The research nurse can be contacted via telephone to solve any (acute) problems that might occur and enters data in RM. The epidemiologist and statistician assist with data analyses and drafting of the manuscript. During the enrollment phase of the trial the coordinating investigator meets bimonthly with the individual principal investigators of the respective centers to assess the current inclusion rate, data quality, protocol adherence and prevalent occurring problems. During enrollment two meetings are planned to collectively assess problems and deliberate on how to instigate solutions to these problems. All participating personnel are updated on a monthly basis via a newsletter in which current inclusion rates are presented, and to point out points of attention and solutions to frequently observed problems. During physical visits CRF’s are collected, assessed for completeness and missing data is retrieved from patient medical records where possible; secondly the appropriateness of administered treatments and (functional) tests is assessed.

### Data monitoring committee

Two independent data monitors are instigated and will monitor the trial at two of the five sites where highest inclusion rates are expected. Results of the monitor will be discussed in a committee independently of the investigators and the investigators will be informed both orally and in writing. Since the overall risk of participation in the trial is considered low by the REC/IRB no external safety overseers are required by national guidelines. If selected, external auditing is possible.

## Outcome parameters

### NRS-pain (primary)

The verbally administered 11-point (range 0–10) NRS-pain is a widely accepted assessment tool and has been validated in many different conditions, among is acute pain in the emergency department [53–55]. Reliability and validity has been thoroughly studied in (cognitively impaired) elderly and has shown to maintain acceptable clinometric characteristics [56–58]. NRS-pain scores are compared within the intervention group i.e. pre and post-treatment and compared between the intervention and control groups. Cumulated pain scores will be calculated for both groups by adding the (post-treatment) pain scores of the first 72 postoperative hours.

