### Standard care

On arrival at the accident and emergency (A&E) department patients receive acetaminophen intravenously, diclofenac (if not contraindicated) and morphine subcutaneously or fentanyl intravenously until numerical rating scale (NRS)-pain scores have dropped below 4. Upon admission the local protocol is started (Table 2). At all centers the 'as needed' medication is administered when the NRS-pain score is 4 or higher and no excessive (opioid-induced) sedation is present. Patients who are deemed able are given intravenous patient controlled analgesia (PCA) pumps with morphine (Table 2). In patients older than 70 years the bolus setting is reduced by 50 %. Preferably patients are operated on using spinal anesthesia. In order to put the patient in an upright position for spinal anesthesia administration femoral blocking with short-acting analgesics can be used. All centers use bupivacaine 0.5 % between 2.0 and 3.0 ml administered at the lumbar level. Additional (long acting) analgesics administered during surgery are noted. The participating centers adhere to the Dutch national guidelines for surgical technique for the various fracture types [43]. Postoperatively, on the day of surgery or the first postoperative day physical therapy is commenced once or twice daily. Physical therapy sessions are usually 30 min long. In the period in which the focus of this study lies physical therapy focuses on strengthening of quadriceps and gluteal musculature, walking and making transfers.

**Table 1 Tab1:** Criteria for participants in the trial

Inclusion criteria	Exclusion criteria
* Intra or extracapsular proximal femur fracture	* Fractures at multiple foci
	* Open fracture/wounds^a^
* Aged 18 years and over	* Acetabular fracture
* Informed consent or proxy consent	* (Suspicion of) concomitant malignancy
	* BMI > 40
	* Unwilling to give proxy consent
	* Preoperative osteosynthesis materials in situ in the ipsilateral leg above knee level
	* Morphine allergy or dependence
	* ASA ≥ 4
	* Cryoglobulinemia
	* M. Raynaud
	* Central neuromuscular disorder
	* Absent ADP/ATP pulsations in the injured extremity
	* Active deep vein thrombosis
	* Suspected pulmonary embolism
	* Patient delay > 24 h
	* NYHA-class ≥ 3
	* IQ-CODE score ≥ 4.6*
	* Long-acting femoral blocks
	* Use of LIA
	* Postoperative HD-instability

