### Study apparatus and treatment schedule

Continuous-flow cryocompression therapy is applied by using the ‘Game Ready system’ (GRS; CoolSystems Alameda, California). Through an anatomically designed hip/groin wrap covering most of the thigh and pelvis up to the iliac crest, the GRS simultaneously delivers both adjustable continuous-flow cryotherapy and intermittent compression through a portable control unit filled with ice and water. The machine has four pressure settings: no pressure, low pressure (5–15 mm Hg), medium pressure (5–50 mm Hg) and high pressure (5–75 mm Hg). Temperature can be adjusted between 4 and 13 °C and is indicated by one, two or three snowflakes. The lowest temperature is started and maintained throughout the study if feasible. Pressure is started at ‘low’ and is increased one step per 4 treatments (Table 3). Depending on the end of surgery patients will be categorized in three treatment schedules with respective start and end-times (Table 3). If patients are uncomfortable the appropriate adjunct will be adjusted stepwise until a comfortable setting is reached, deviations are noted. Adjustments are recorded and comfortable settings are maintained according to the discomfort flowchart (Fig. 2). Patients will be treated between 10 and 12 times during the first 72 postoperative hours, each cycle lasting 30 min. Preferably, treatment cycles and control measurements during the first 72 postoperative hours are performed at fixed moments: 8:00 h, 12:00 h, 16:30 h, and 21:30 h. The GRS-wrap is only in place when CFC therapy is administered and applied/removed by the nurse.

**Table 3 Tab3:** Treatment schedule and pressure settings

End time surgery	Schedule	Start time										
10:00 – 16:00 h	*A*	16:30 h										
16:00 – 21:00 h	*B*	21:30 h										
>21:00 h	*C*	8:00 h										
Cycle no. →	1	2	3	4	5	6	7	8	9	10	11	12
OK + 0	*A:* – Low	*A* – Low										
	*B: –* Low	-										
	-	-										
OK + 1	-	*-*	*A* – Low	*A* – Low	*A* – Med	*A* – Med						
	-	*B –* Low	*B –* Low	*B –* Low	*B –* Med	-						
	*C* – Low	*C* – Low	C – Low	*C* – Low	-	-						
OK + 2					*-*	*-*	*A* – Med	*A* – Med	*A –* High	*A –* High		
					*-*	*B –* Med	*B –* Med	*B –* Med	*B* – High	-		
					*C –* Med	*C –* Med	*C –* Med	*C –* Med	-	-		
OK + 3									-	*-*	*A –* High	*A –* High
									-	*B* – High	*B* – High	*B* – High
									*C –* High	*C –* High	*C –* High	*C –* High

Regular treatment times: 8:00 h; 12:00 h; 16:30 h; 21:30 h

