### Cryocompression therapy and clinical measurements

Intervention patients start with CFC therapy 6 h postoperative, until 72 h postoperatively. A trained ward nurse will conduct the pain assessments when the patient is in bed or stationary in a chair for at least five minutes. Directly before and directly after CFC therapy vital signs including NRS-pain are measured by the ward nurse, when the patient is prone in bed for at least five minutes before commencing and five minutes after cessation of CFC therapy. In control patients only NRS-pain is measured at the same time as intervention patients would normally be assessed. All pain measurements are continued throughout the first postoperative 72 h for control and intervention patients alike (Table 4). Three times daily DOS-scores [48] will be obtained; in case of a DOS-score higher or equal to three, geriatricians diagnose and subsequently monitor delirium severity with the delirium rating scale revised 1998 (DRS-R-98) [49] on a daily basis or until the score drops below 12.25 out of 39 (Table 4). Time and amount of administered (psychotropic) medication will be documented. The nurse and ward doctor inspect the wound and dressing in accordance with routine care. Blood samples are taken at postoperative day one and three, and post-transfusion if applicable (Table 4). The timed up and go test (TUGT) is performed before discharge (Table 4). The TUGT will be administered in all patients who are able. If no weight bearing is allowed or patients are physically unable, than the test will be postponed to the outpatient visit. The mini mental state examination (MMSE) is administered for data stratification purposes [50–52], if patients are delirious during admission the MMSE is postponed to the outpatient visit.

In order to document experiences with CFC therapy all treatment patients will fill in a questionnaire at discharge, which is specifically drafted for this study (Table 5). During the study a booklet will be made available into which staff can write down prevalent occurring technical GRS-related problems.

**Table 5 Tab5:** Patient questionnaire

1. Did you feel that the pain reduced when treated with cryocompression therapy?	A	B	C	D	E
2. Would you rather have cryocompression treatment than analgesic pain treatment?	A	B	C	D	E
3. The standard setting used was the coldest; did you like this temperature setting?	A	B	C	D	E
4. Did you request the temperature setting to be upped?	Y				N

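### The cumulated 72-h pain score counts only post-session readings in the cryocompression arm, so it records the short-lived effect of a session rather than pain over 72 h, and it favours that arm if controls are scored only at the fixed moments

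*Protocol article*

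**What the plan says.** The stated aim is pain in the first 72 postoperative hours. Under NRS-pain (primary), the one 72-h summary score is defined as follows: "Cumulated pain scores will be calculated for both groups by adding the (post-treatment) pain scores of the first 72 postoperative hours". The same section announces a pre/post comparison within the CFC arm and a comparison between arms.

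The section Cryocompression therapy and clinical measurements sets the timing in the CFC arm: "Directly before and directly after CFC therapy vital signs including NRS-pain are measured by the ward nurse", with bed rest "five minutes before commencing and five minutes after cessation of CFC therapy". For controls it says: "In control patients only NRS-pain is measured at the same time as intervention patients would normally be assessed". It requires nurses to "conduct the pain assessments when the patient is in bed or stationary in a chair for at least five minutes", and it continues pain measurement to 72 h in both arms.

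Study apparatus and treatment schedule says that, preferably, "treatment cycles and control measurements during the first 72 postoperative hours are performed at fixed moments", namely 8:00, 12:00, 16:30 and 21:30 h. It also says: "Patients will be treated between 10 and 12 times during the first 72 postoperative hours, each cycle lasting 30 min". Table 3 lists 12 cycles for each of its three schedules.

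The primary analysis (Analysis of outcome parameters) and the sample size calculation both use NRS-pain at 24 h, with a mixed model for the course over time. Neither says whether the CFC reading is the one before or the one after a session.

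**The concern.** The plan records two readings per session in the CFC arm and puts only the second into the sum. That reading comes when any effect of cold and compression should be near its greatest. Controls have no treatment, and on the plainest reading of the schedule their score falls at the fixed moment when a CFC session begins. The sum would then set the best moment of each CFC cycle against an ordinary moment in controls, and the result would be presented as pain over 72 h.

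The second weakness is the raw sum. Every lost score lowers the total, so missing data look like pain relief. If CFC patients who refuse or stop sessions lose their post-treatment scores, poor tolerance would count in favour of the device.

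The same unstated choice of reading carries over to the 24-h comparison. The trial is open-label, so the choice should be fixed before anyone sees data.

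**Working it through.** **Plan's own figure.** Inputs from Sample size calculation: SD 2.2, difference 1.3, alpha 5 % (taken as two-sided), power 90 %, dropout 22.3 %. Normal approximation: n per arm = 2(1.960 + 1.282)² × 2.2² / 1.3² = 60.2, so 61. The t-based calculation gives 62 per arm, 124 in total, and 124 / (1 − 0.223) = 159.6, so 160. The stated 160 is reproduced. It rests on the 24-h score, so nothing below changes it.

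**How much of the 72 h the sum samples.** 12 sessions × 0.5 h = 6 h, and 6 / 72 = 8.3 %. Every CFC score in the sum is taken just after one of these periods.

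**What a short dip does to the sum.** Assume a drop of d points that is seen at the post-session reading, has gone by the next fixed moment, and has no counterpart in the control reading. The sum shifts by 12 × d. If the drop lasts h hours after the session, the true difference in 72-h mean pain is 12 × d × h / 72 = d × h / 6. For the chance of p < 0.05, take 62 per arm, SD 2.2 and within-patient correlation r from 0.3 to 0.7 (assumed). The SD of the sum is 12 × 2.2 × √(r + (1 − r)/12), which is 15.8, 19.4 and 22.5 for r = 0.3, 0.5 and 0.7.

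| d (assumed) | Shift in sum | Chance of p < 0.05 | True 72-h mean difference, h = 0.5 to 2 |
|---|---|---|---|
| 0.5 | 6.0 | 32–56 % | 0.04–0.17 |
| 1.0 | 12.0 | 84–99 % | 0.08–0.33 |
| 1.3 | 15.6 | 97–100 % | 0.11–0.43 |

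The sum divided by 12 exceeds the true 72-h difference by a factor of 6 / h, whatever the dip: 12, 6 or 3 for h = 0.5, 1 or 2. If the full drop is also credited to the 30 session minutes, the factor is 6 / (h + 0.5): 6, 4 or 2.4. These are not false-positive rates, because a brief real effect is present. They show that the sum can be clearly significant when 72-h pain hardly differs.

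**Does a varying number of cycles bias the sum?** The schedule depends on when surgery ends, and 1:1 randomization follows surgery, so the count is set before allocation. With 10 to 12 scores drawn alike in both arms (mean NRS 4 and r = 0.5 assumed, 20,000 simulated trials), the difference is −0.02 points and the type I error 5.3 %. That is noise, not bias.

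**Does unequal loss of scores bias it?** In the same simulation, with CFC patients losing one score each on average and controls none, the sum falls by about 4 points (1 × mean NRS 4). Then p < 0.05 occurs in about 24 % of trials with no effect.

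**The case against.** The strongest reply has four parts.

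- The control sentence follows directly on the one that sets readings before and after each session. It can be read as scoring controls at both clock times, without the other vital signs. This stands as a possible reading, and the bias between arms is therefore conditional. Matching the clock would not turn a sum of post-session readings into a measure of 72-h pain.
- Pain measurement continues to 72 h in both arms and the analysis is by intention to treat, so a patient who stops CFC need not lose scores. This stands in part. The article keeps the measurements going but does not say that a reading without a delivered session enters a sum of post-treatment scores.
- Controls also rest for at least five minutes before scoring. This stands. The contrast in rest is about 40 minutes (5 + 30 + 5) against at least five, not rest against none.
- The score is not the powered analysis, and pre-session readings alone would be selective the other way: they fall 4 to 10.5 h after the previous session began. Both parts stand. The remedy should therefore not rest on pre-session scores alone wherever matched later readings exist.

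A reader might also infer that as-needed analgesia inflates the CFC result, since such "medication is administered when the NRS-pain score is 4 or higher" and a pre-session score could trigger a dose that acts before the post-session score. The article does not say that doses are given in that interval, and the threshold applies to both arms. This is a possibility to keep in mind for the pre/post comparison, not an established bias.

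**Conclusion.** The point holds in a limited form. As defined, the cumulated score measures the immediate post-session effect and not pain over 72 h. It favours CFC if controls are scored only at the fixed moments. Under the assumed dips, it overstates the 72-h difference about 3- to 12-fold, or 2.4- to 6-fold if the session itself is counted. Dip size, duration, correlation and mean NRS are assumptions, not figures from the article.

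Two stronger readings are tempting and not supported. One is that the varying number of cycles itself biases the sum towards CFC. It does not, because the count is set before randomization; only unequal loss of scores between arms is directional. The other is that the trial's primary result is compromised. The powered analysis is NRS at 24 h, and the cumulated score is supportive. The 24-h comparison is affected only in that the article does not state which CFC reading it uses.

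Separately, the text gives 10 to 12 cycles and Table 3 gives 12 for every schedule, so the number of planned scores is not settled. Counting sessions completed within 72 h gives 11 or 12 from the Table 3 start times, and 10 to 12 from the 6-h start given under Cryocompression therapy and clinical measurements.

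**What to change.** 1. Replace the sum by a time-weighted mean NRS over all scheduled moments to 72 h, and include the pre-session scores already recorded in the CFC arm.
2. State at which clock times controls are scored, and compare only like-timed readings. If controls have both readings, use both in each arm, with stated weights. If they have only the fixed moment, compare it with the CFC pre-session reading.
3. Keep all scores at scheduled moments after CFC is stopped or a session is skipped.
4. Use the score before cycle 1 as a covariate, not as part of the outcome.
5. For the 24-h comparison, name the same like-timed reading: pre-session in the CFC arm, matching the control fixed moment.
6. Report post-minus-pre change within the CFC arm as descriptive only.
7. Reconcile the number of cycles and the start time between the text and Table 3.

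The cost is mainly analysis wording. The CFC pre-session scores are already collected and N = 160 is unaffected. Adding a later control reading, if there is none, would change study procedures and so need an amendment under the article's own dissemination policy. The real downside is that the contrast between arms may be smaller, most of all where only pre-session readings can be matched.
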